## Abstract

**Background:**

Children with cerebral palsy receive a variety of long-term physical and occupational therapy interventions to facilitate development and to enhance functional independence in movement, self-care, play, school activities and leisure. Considerable human and financial resources are directed at the "intervention" of the problems of cerebral palsy, although the available evidence supporting current interventions is inconclusive. A considerable degree of uncertainty remains about the appropriate therapeutic approaches to manage the habilitation of children with cerebral palsy. The primary objective of this project is to conduct a multi-site randomized clinical trial to evaluate the efficacy of a task/context-focused approach compared to a child-focused remediation approach in improving performance of functional tasks and mobility, increasing participation in everyday activities, and improving quality of life in children 12 months to 5 years of age who have cerebral palsy.

**Method/Design:**

A multi-centred randomized controlled trial research design will be used. Children will be recruited from a representative sample of children attending publicly-funded regional children's rehabilitation centers serving children with disabilities in Ontario and Alberta in Canada. Target sample size is 220 children with cerebral palsy aged 12 months to 5 years at recruitment date. Therapists are randomly assigned to deliver either a context-focused approach or a child-focused approach. Children follow their therapist into their treatment arm. Outcomes will be evaluated at baseline, after 6 months of treatment and at a 3-month follow-up period. Outcomes represent the components of the International Classification of Functioning, Disability and Health, including body function and structure (range of motion), activities (performance of functional tasks, motor function), participation (involvement in formal and informal activities), and environment (parent perceptions of care, parental empowerment).

**Discussion:**

This paper presents the background information, design and protocol for a randomized controlled trial comparing a task/context-focused approach to a child-focused remediation approach in improving functional outcomes for young children with cerebral palsy.

**Trial registration:**

[clinical trial registration #: NCT00469872]

## Background

Cerebral palsy comprises a complex, multi-dimensional group of non-progressive movement disorders resulting from damage to the brain prenatally, perinatally, or early in childhood. Incidence of cerebral palsy has remained constant over the past two decades at 2.0 to 2.5 per 1000 live births [1,2]. The long-term disability and costs to the health care system and society associated with cerebral palsy are significant. Cost of services to these children and their families is substantial, with health costs alone estimated at $1,406 per family per year (over $6 billion per year) [3]. Non-reimbursed costs to families for services, equipment, and lost family income can amount to thousands of dollars each year [4]. Honeycutt et al. [5] state that the extra economic lifetime costs associated with cerebral palsy is $800,000 per person.

From the viewpoint of the International Classification of Functioning, Disability and Health (ICF) [6], cerebral palsy presents with "impairments" in body function and structure such as muscle tone, strength, reflexes and range of motion. Significant "activity" limitations can also be present (e.g., dressing, feeding, functional mobility) as well as restricted "participation" (e.g., playing, participating in school) in social and community roles for the child.

This project, coordinated from *CanChild *Centre for Childhood Disability Research at McMaster University, Hamilton, Canada builds on research conducted by our research team over the past several years to develop and test a task/context-focused approach to treatment for young children with cerebral palsy.

The primary objective of this project is to conduct a multi-site randomized clinical trial to evaluate the efficacy of a task/context-focused approach compared to a child-focused remediation approach in improving performance of functional tasks and mobility, increasing participation in everyday activities, and improving quality of life in children 12 months to 5 years of age who have cerebral palsy.

In North America, neurodevelopmental treatment is the most commonly used treatment technique used by therapists in their care of children with a diagnosis of cerebral palsy [7]. Although this approach acknowledges functional independence as an important goal of treatment [8,9], the means to obtain function focuses on remediation of the child in the International Classification of Functioning, Disability and Health (ICF) component of body function and structure. The therapist attempts to inhibit abnormal posture and movement and to improve the child's quality and efficiency of movement by encouraging typical patterns of movement [10,11]. It is assumed that "typical" patterns of movement will lead to functional improvements and reduce activity limitations and participation restrictions. Research to support this assumption is inconclusive [12].

Some therapists and researchers are questioning this emphasis on "normality" because it may not explore all options for functional success [13-17]. Compensatory movements and environmental adaptations may be more efficient solutions to the motor challenges encountered by children with cerebral palsy [18-20]. From this latter perspective, performing the functional task, rather than attainment of normal patterns of movement, is the important goal of treatment.

An array of factors has influenced this philosophical shift – including current models of health status, the perspectives of persons with disabilities, family-centered service delivery, and the application of dynamic systems theory (DST) to motor behavior. Each concept is discussed briefly here.

### (a) Models of health status

Therapists are now using models of health status, such as the ICF [6], as frameworks to identify primary goals, and to evaluate treatment effects. These models have provided a framework by which to discuss and question the assumption of a cause and effect relationship between impairments and functional restrictions [6,21,22]. Functional performance is the result of the dynamic interaction of a myriad of factors, not just those at the level of impairment within the child. The new component of contextual factors in the ICF model encourages therapists to consider the influence of personal and environmental attributes on function simultaneously with the physical abilities of the person. The concept that many factors both internal and external to the child influence functional motor success has caused a re-evaluation of current treatment approaches based on a hierarchical neuromaturational model focused primarily on changing the child's abilities.

### (b) Influence of persons with disabilities

Changing societal attitudes towards disability complement the health status frameworks used in this study. Traditionally, disability was viewed as a problem within the person and the goal was to fix, heal or prevent the problem [23]. Persons with disabilities advocated for a change in this perspective, suggesting that disability is a political rather than a medical issue. The social construction model of disability put forward that society's values and beliefs artificially partition persons into 'disabled' and 'able-bodied' roles in society, and prevent the full participation of persons with disabilities in the community [23-27].

### (c) Family-centered principles

The development of the family-centered philosophy in rehabilitation practice has also influenced attitude changes in the management of children with motor dysfunction. Family-centered service principles clearly articulate that parents know their children best. Family-centered service acknowledges that families are different and unique, and that optimal child functioning occurs within a supportive family and community context [28]. Within this framework, the therapist is viewed as a collaborator, not an expert. Goals of treatment are identified collaboratively with input from the family, child and therapist. This change in service delivery has created an environment conducive to the identification of functional goals at the level of activity and participation rather than exclusively at the level of impairment. There is a need to explore all treatment strategies, including changes to the task and environment, in order to facilitate the achievement of these goals.

### (d) Dynamic Systems Theory

Dynamic Systems Theory (DST) is a recent framework to explain motor development [29,30]. DST suggests that the most efficient motor behavior results from the spontaneous self-organization and interaction of many subsystems to achieve a functional goal. These subsystems derive from three sources: the child, the task and the environment [31]. Within the child, subsystems include not only the central nervous system, but also factors such as biomechanics, anthropometric measures (e.g., head size), temperament, and cognition. Examples of subsystems within the task (what the child is trying to do) which affect motor behavior, are the shape of an object being grasped, or the height of a table that the child uses to pull to stand. In the environment, diverse factors such as the surface on which the child is moving, the effect of gravity and the child's interaction with caregivers or therapists may contribute to the motor behavior that emerges.

The concept that spontaneous self-organization results in the best movement solution challenges therapists to reconsider the traditional therapeutic rejection of "abnormal" movement patterns such as "bunny-hopping" and "W-sitting" that many children with cerebral palsy spontaneously discover and use effectively. Historically, therapists have discouraged these "abnormal" movement patterns because of concern that they would prevent the emergence of more typical ways to move and sit and might result in decreased range of motion. Should these movement solutions be discouraged or accepted as innovative solutions? DST theory challenges traditional treatment perspective that "typical" patterns of movements are the optimal solution for all children. New treatment models are emerging that consider functional success the goal of treatment with less concern about the "normality" of the movement strategy [18,20,32,33].

From a DST perspective, adaptation of the environment and/or task is acceptable as a solution to a motor problem rather than immediately focusing on changing the abilities of the child. Burton and Davis' [34] ecological task assessment is based on matching the task and environment with the abilities of the child in order for the child to achieve success, instead of trying to change the child to conform to an existing environment. For example, rather than viewing walking as the optimal mobility method, some therapists now advocate an array of movement options for children with cerebral palsy that represent the best fit with specific environments [35].

### Integrating these themes – the Task/Context-Focused Approach

The following principles define the key components of the task/context-focused approach.

#### 1. Promote Functional Performance

The goal of treatment is for the child successfully to achieve a specific functional goal that has been identified collaboratively by the family, child and therapist. Emphasis is placed on success with the task rather than the attainment of "normal" patterns of movement. The underlying principle is that there is no one right way to perform a task. Different solutions may be used in different environments. For example, if the goal is for the child to move independently in the home, the child may creep on his or her abdomen on the smooth surface of the kitchen floor but change to rolling on the carpet in the living room. This principle is derived from the DST tenet that movement is always goal-oriented and context specific.

#### 2. Identify Periods of Change (Transition)

Treatment will be most successful if it is introduced at a time when the child is trying to do a new task or attempting to do an established task in a different way. This premise fits with the concept of a developmental, global readiness for performing a new motor task or changing the way an established task is accomplished. Parents (and child) will play an integral role in deciding when the child is ready to attempt a new skill. Transition is a concept of DST that is defined kinematically as the period when a child's movement patterns are more easily perturbed and take longer to return to a stable state. Clinically, the concept of transition is intriguing because it implies a "window of opportunity" when a child is most ready to achieve new functional goals. A study by Trahan & Malouin [36] provides evidence that short term intensive therapy at this "right time" may be as effective as longer term, regular therapy. In a multiple baseline design, five children with cerebral palsy who received short periods of intensive therapy (4 times/week for 4 weeks) followed by no therapy for 8 weeks maintained gains in their motor skills. Using transition as an indicator of readiness, treatment will be time-limited and aimed specifically at success on an identified functional goal.

#### 3. Identify and Change the Primary Constraints

Constraints or rate-limiting factors that prevent achievement of a functional goal are identified. Treatment strategies will be based on the identification of both constraints and enablers of a specific goal by the parents, child and therapist. These constraints and enablers may be identified in the child, the task (goal) or the environment. For each constraint, the therapist must consider if the specific constraint can be changed or whether an adaptation is needed. Examples within the environment are the effects of gravity, space to move, floor surface etc. Examples of how the task may be changed are changing the size of the spoon for a feeding goal and modifying a walker for a mobility goal. Examples of constraints within the child are muscle strength, range of motion, motivation. Constraints/enablers associated with the task and/or the environment will be the first focus of treatment before attempts to change constraints within the child. If a specific changeable constraint is identified within the child, intervention may include changing this constraint through time-limited intervention but only at the level of activity and/or participation. This approach is different from a child-focused approach that centers on remediation of the abilities of the child, usually at the level of body structure and function. The aim of the task/context-focused treatment is to achieve success at the functional goal as soon as possible rather than emphasize the quality of a child's movement.

#### 4. Provide Opportunities for Practice

Children will have opportunities to practice a new skill in the most appropriate environment. Sometimes skills will emerge spontaneously when an appropriate constraint has been changed, but typically in childhood, developmental skills require practice for refinement and to become more automatic. If necessary, practice will be incorporated into the treatment. Again, the emphasis will be on achievement of the functional goal in a natural setting. Practice focuses on the functional goal in the most appropriate environment [37].

### The Child-Focused Approach

A review of the literature in children's rehabilitation in preparation for this project yielded 77 papers reporting research that involved children with cerebral palsy. A wide variety of treatment approaches are being used with this population including surgical treatments such as tendon transfers [38] and dorsal rhizotomy [39,40] and pharmacological treatments, most typically, botulinum toxin injections and intrathecal baclofen [7,41,42].

Treatment approaches utilized by physical and occupational therapists focus primarily on remediation of body function and structure in children with cerebral palsy. These treatments include: maintaining range of motion and joint alignment through stretching, casting and splinting [43,44], strength training [45-47], facilitation of normal movement patterns and postural control through physical handling and practice of functional activities [12,48,49], treadmill training [50] and electrical nerve stimulation [51,52]. Adaptive equipment is frequently prescribed for seating, positioning, mobility and function [53,54]. Only four articles were found that evaluated a functional therapy approach [33,37,55,56].

The therapy literature describing treatment approaches continues to emphasize neurodevelopmental approaches, primarily aimed at changing body function and structure in the child. Treatment now embraces tenets of motor learning and systems theories applied to movement. For example, identification of functional goals and the importance of the child taking control of movements [8] are now both incorporated as important components. However, the means to attain these goals still emphasize changing the child's quality of movement, with typical movement patterns used as the "gold standard" [10,11]. Improvements in functional performance are frequently cited as the desired outcome; however, the methods for achieving this outcome are primarily through changes in body function and structure within the child [57,58].

## Methods/Design

The goal of this randomized controlled cluster design trial is to evaluate the efficacy of the task/context-focused approach with young children ages 12 months to 5 years 11 months with cerebral palsy compared to a child-focused approach to improve performance of functional tasks, mobility, participation in everyday activities, and quality of life. We will recruit a population-based sample of 220 children with cerebral palsy ages 12 months to 5 years 11 months at recruitment date.

The research ethics boards at McMaster University, the University of Alberta, the Calgary Health Region and all participating centres granted approval for the study. The study has a data and safety monitoring plan, which includes a Data and Safety Monitoring Board (DSMB) as per NIH procedures for multi-site clinical trials. All participants will be informed that their participation is voluntary and that they can withdraw at any time without affecting their regular health care. Parents will be asked to read and sign a consent form for the project. The trial intervention period is 6 months in duration and poses no known risks to study participants. One unlikely risk may be that children lose range of motion in certain joints that may ultimately affect their motor function. To ensure that there are no adverse restrictions in range of motion from either treatment, range of motion will be evaluated for all children at baseline, and 3, 6, and 9 months. If a child's range decreases by 8–10 degrees, the absolute magnitude of the current ROM will be examined. If the current absolute value of the range is clinically worrisome, the child's treating therapist will be contacted. He/she will measure the joint again. If ROM remains worrisome, the site coordinator will be notified and will arrange for a physician referral. Any stretching intervention implemented will be recorded and the child will remain involved in the study and included in the analysis, even if therapy is modified.

### Study sample

Children will be recruited from a representative sample of children attending publicly-funded regional children's rehabilitation centers serving children with disabilities in Ontario and Alberta, Canada. Because the Canadian health system enables all citizens to have universal and equal access to publicly-funded services, and because virtually all children with cerebral palsy are served in the programs that will be participating in the study, the sample recruited from the services and programs described above is expected to be fully representative of children with cerebral palsy. 24 centers, 16 in Alberta and 8 in Ontario, will participate.

### Inclusion criteria

▸ Children of either sex with diagnosis of cerebral palsy based on published diagnostic criteria [59]

▸ Children classified in Levels I-V on the Gross Motor Function Classification System (GMFCS) (as determined by their current therapist)

▸ Children aged 12 months to 5 years 11 months at the time of recruitment

▸ Some of the younger children might not yet have an official diagnosis of cerebral palsy. Therapists will be asked to identify suitable children for the study using a screening criteria checklist for children with significant developmental motor delays, which was used in a previous study. These children will have a confirmed diagnosis of cerebral palsy upon exit from the study.

### Exclusion criteria

▸ Children with planned surgical intervention or medication changes during the study period that may affect motor function.

▸ Children whose families feel uncomfortable or unable to respond to interviews and questionnaires in English (the language of virtually all the study materials). Our experience in previous research has shown that less than 5% will be excluded on this criterion.

▸ Since this an efficacy study, parents or caregivers who state that they will not be able to adhere to the treatment schedule will not be entered in the study.

### Sample size

Sample size was calculated for the primary study outcome, using the following: where n = number of subjects per group, **α **= significance level (2-sided testing), **1 - β **= power, **σ **= SD of change within individuals, ICC = intraclass correlation, m = average cluster size, **Δ **= minimum absolute change to be detected, number of clusters (therapists) = n/m. The within-child standard deviation for change on the PEDI scale was set at 7. This value is based on data reported in the PEDI manual, and data from Ketelaar et al. [33]. Specifically, the value 7 is the working average of the within-child standard deviation observed by Ketelaar et al. [33] for self-care functional skills and mobility. We took the average cluster (number of children per therapist) size to be 3, the ICC to be 0.1, and therefore assumed a variance inflation factor (design effect) associated with therapists to be 1.2. The variance inflation factor allows for the possibility that some therapists may be more effective in inducing a change on the PEDI scale compared to other therapists, and takes into account the clustered nature of the sample of participating children. Based on data from our task/context-focused pilot study, we projected an estimated difference in the change scores between the treatment groups of 3 points on the PEDI, and used a two -sided α-value of 0.05, with power of 80%. Our sample size estimates are based on the PEDI because it demonstrates the greatest score variability, and because it is the primary measure of interest in the study. The specifications above lead to a required sample size of 104 children per group, which we rounded to 105 per group so that 35 therapists would be required per group. With additional children to account for dropouts, our target sample size is set at 220.

### Recruitment procedure

Each center in the study has a site coordinator who contacts all therapists to inform them about the study and to obtain their consent to participate. Once therapists have consented to participate in the study they will be block randomized by the coordinating site (by OT or PT discipline) into either treatment arm. On behalf of the research team, each center in the study will mail information that will describe the study to eligible families. Families will be asked to read over the information and indicate their interest in the study on a form to be returned to the research center in a stamped self-addressed envelope. At the baseline visit, study assessors will review the information sheet with the families and witness and co-sign the consent form. Assessors will leave a signed (carbon) copy of the consent form with the family.

Children from consenting families will follow their therapist into the treatment arm that the therapist was randomly assigned to. Due to the nature of the therapy, it will not be possible to keep therapists or parents unaware of the child's treatment group. Therefore, trained, reliable evaluators who are blinded to group assignment will measure all outcomes. Evaluations will be completed at baseline, after 6 months, and at a 3-month follow-up.

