### Measure and data collection procedures

The primary outcome in this study is performance of functional tasks (mobility and self-care) as measured by the Pediatric Evaluation of Disability Inventory (PEDI) [65]. Secondary outcomes include range of motion, gross motor function, participation in everyday activities, health status, parent empowerment, and parents' perceptions of care. Independent evaluators who are unaware of the child's treatment assignment will assess the children and parents/caregivers in their home. Outcome measures in the trial include:

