### Activities

#### 1. Pediatric Evaluation of Disability Inventory (PEDI)

The Pediatric Evaluation of Disability Inventory (PEDI) [65] will be used to measure mobility and self-care. The PEDI can be completed by structured interview. Part I: Functional Skills and Part II: Caregiver Assistance will be administered for the Mobility and Self-care Domains. Internal consistency measured by Cronbach's alpha is .99 for the Self-Care domain and .97 for the Mobility domain. Inter-rater reliability (ICC) between interviewers is 1.00 for both domains among rehabilitation therapists; and .88 and .98 when completed by different family members. Evidence of concurrent validity is provided by the high correlations between the Self-Care domain and Wee-FIM Self-Care scores (r = .92) and Mobility domain and Wee-FIM Mobility scores (r = .97). Responsiveness of the PEDI for children with CP was demonstrated over a 4–6 month period for the Self-care and Mobility Domains when assessed by a therapist and in the Self-care Domain when assessed by a parent [67].

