#### 2. Gross Motor Function Measure (GMFM-88)

The 88-item version of the GMFM includes five dimensions (Prone and Supine; Sitting; Crawling and Kneeling; Standing; Walking, Running and Jumping). Each item is measured by observation and scored on a 4-point ordinal scale. The GMFM is the gold-standard measure used in clinical trials for children with cerebral palsy. Validation of the GMFM for children with cerebral palsy was first published in 1989 [68]. Additional evidence of validity and responsiveness of the GMFM for children with spastic diplegia and quadriplegia has also been established [69]. Several studies have documented the test-retest and inter-rater reliability of the 88-item GMFM [69-71]. Inter-rater reliability ranges from 0.87 to 0.99 and test-retest reliability ranges between 0.76 to 0.99

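### Blinded evaluators do not blind the primary PEDI: its informant is, by strong inference, a parent who knows the arm, so the stated safeguard covers only the observed and measured outcomes

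*Protocol article*

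**What the plan says.** The Recruitment procedure section of the protocol article accepts that "it will not be possible to keep therapists or parents unaware of the child's treatment group". It draws the consequence in the next sentence: "Therefore, trained, reliable evaluators who are blinded to group assignment will measure all outcomes". The section on measures and data collection repeats that evaluators are unaware of assignment and says they "will assess the children and parents/caregivers in their home".

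That section also names the primary outcome: "The primary outcome in this study is performance of functional tasks (mobility and self-care) as measured by the Pediatric Evaluation of Disability Inventory (PEDI"). On how the PEDI is obtained, the article says "The PEDI can be completed by structured interview", and that "Part I: Functional Skills and Part II: Caregiver Assistance will be administered for the Mobility and Self-care Domains". It names no informant and describes no observation of the child for this instrument. For the GMFM-88, by contrast, it says "Each item is measured by observation and scored on a 4-point ordinal scale". Range of motion is measured by goniometer, each range twice and averaged. The PedsQL CP Module form for ages 2 to 4 is described as a parent report.

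**The concern.** The blinding sentence is offered as the answer to unblinded parents. A blinded evaluator removes the evaluator's own bias, but not that of the person who supplies the answers. If a parent who knows the arm tells the evaluator what the child can do and how much help is needed, the PEDI score carries the parent's knowledge of the arm.

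The design also gives a specific reason why parents' expectations might differ between arms. In Table 1 the parent defines the goals in the context-focused arm, using the COPM, whereas the therapist sets them, after discussion, in the child-focused arm. Parents in the context-focused arm also take part in analysing the videotaped task and identifying constraints. They would then report on functional self-care and mobility tasks, the level at which their goals were set.

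At stake is the reading of the primary result. A reader who takes the sentence at face value would treat a PEDI benefit as a blinded finding, when differential reporting remains a possible explanation.

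**Working it through.** **Step 1: who supplies the PEDI data.** No sentence names the informant. Four statements in the article point the same way:

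- Children are 12 months to 5 years 11 months at recruitment (Inclusion criteria), too young to be the respondent to a functional inventory.
- Families not comfortable or able to answer interviews and questionnaires in English are excluded (Exclusion criteria), so families are the expected respondents.
- Evaluators assess parents or caregivers as well as children, at home (Measure and data collection procedures).
- The PEDI is described as an interview, the GMFM-88 as observation.

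A parent informant is therefore a strong inference. The other plausible informant, the treating therapist, is also unblinded, so the conclusion does not depend on which of the two it is.

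**Step 2: which outcomes the safeguard covers.**

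| Outcome | Source of the data | Is the source blinded? |
|---|---|---|
| Range of motion | Goniometry by the evaluator | Yes |
| GMFM-88 | Observation by the evaluator | Yes |
| PEDI (primary) | Interview, parent by inference | No |
| PedsQL CP Module, toddler form | Parent report, stated | No |
| Family empowerment, perceptions of care | Parents' own views | No |

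**Step 3: the plan's own figure.** Inputs from the Sample size section: SD of change 7, difference 3, two-sided alpha 0.05, power 80%, cluster size 3, ICC 0.1.

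- Without clustering: n = 2 × [7 × (1.960 + 0.842) / 3]² = 85.5, rounded up to 86 per group.
- Design effect: 1 + (3 − 1) × 0.1 = 1.2.
- 86 × 1.2 = 103.2, rounded up to 104 per group.

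This matches the stated 104, which the plan rounds to 105. Power at 105 per group is 80.9%. No stated number is in error.

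**Step 4: illustration of what a reporting bias would do.** The standard error of the between-arm contrast is √(2 × 7² × 1.2 / 105) = √1.12 = 1.058 points. With no true effect and a differential reporting bias of b points, the two-sided rejection rate is Φ(b/1.058 − 1.96) + Φ(−b/1.058 − 1.96):

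| Assumed bias b (PEDI points) | Share of the 3-point target | False-positive rate |
|---|---|---|
| 0 | 0 | 5.0% |
| 0.5 | one sixth | 7.6% |
| 1 | one third | 15.7% |
| 2 | two thirds | 47.2% |

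The bias sizes are assumptions; the documents give none. The calculation is symmetric, so bias towards either arm gives the same rates.

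**The case against.** **The blinding sentence is literally true.** The evaluators are blinded, and the preceding sentence discloses that parents and therapists are not. This stands as far as it goes. But the two sentences are joined as problem and remedy, and for interview data the remedy does not reach the problem.

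**The parent informant is not stated.** Also true; it is an inference and should be called one. A condensed article may leave administration details to the full protocol or the instrument manual, so no fault is found here for not saying whether the same respondent is used at every visit.

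**Both arms are active.** Each receives 18–24 sessions and parent education, and parents are consulted on goals in the child-focused arm too. COPM goals are not the outcome. So neither the size nor the direction of any bias is known, and Step 4 shows only what a bias of a given size would do.

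**Stronger readings that the documents do not support:**

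- A reader might infer that Mobility is collected by a mode not shown to be responsive, since the cited evidence covers both domains when a therapist assesses but is given only "in the Self-care Domain when assessed by a parent". The article does not settle whether an interview led by a trained evaluator counts as assessment by a therapist or by a parent, and absence of cited evidence is not evidence of unresponsiveness.
- A reader might set the reliability of 1.00 among rehabilitation therapists against .88 and .98 for family members. The first is agreement between interviewers; the others apply when different family members complete the instrument. The comparison is not like for like.
- A reader might want a PEDI benefit to count only if the GMFM-88 points the same way. The context-focused approach does not aim at hierarchical motor skills or movement quality, and the GMFM-88 does not measure self-care, so a real PEDI gain without a GMFM-88 gain fits the treatment's rationale. If the true GMFM-88 effect were zero and the two estimates independent (assumptions), such a rule would cut power from 80.9% to 0.809 × 0.5, about 40%.
- Scoring some PEDI Mobility items from observation would mix modes within one scale, might no longer fit the assumed SD of 7 and difference of 3, and would leave Self-care unprotected.

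**Conclusion.** The concern holds in a limited form. The article presents evaluator blinding as protecting all outcomes, but it protects only those that the evaluator observes or measures: GMFM-88 and range of motion. For the primary PEDI the evaluator is blinded and the informant, by strong inference, is not. For the PedsQL toddler form an unblinded source follows directly from the text.

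This does not show that the PEDI result will be biased. It shows that the design lacks a property that the article claims for it. The possible size is not trivial on the plan's own inputs: an assumed 1-point differential, a third of the target difference, would roughly triple the false-positive rate, from 5% to about 16%. That figure rests on the planned SD, the design effect of 1.2, 105 children analysed per arm, a single PEDI change score and an assumed bias.

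**What to change.** 1. **Correct the blinding statement** in the Recruitment procedure section and in the section on measures and data collection. Suggested sense: *Evaluators are unaware of group assignment. GMFM-88 and range of motion are blinded observations or measurements. The PEDI and the other parent-reported measures are collected or administered by blinded evaluators from parents or caregivers who know the child's treatment group.* If the PEDI informant is someone other than the parent, name that person and state whether he or she is blinded.

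2. **State in advance how a PEDI benefit will be presented.** Name the GMFM-88 as the key supporting secondary outcome and report its between-arm contrast, with confidence interval, beside the PEDI contrast. If only the PEDI shows benefit, acknowledge reporting bias as a possible explanation. The direction of the GMFM-88 contrast should not be a condition for claiming efficacy, and the way the PEDI is scored should stay as planned.

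**Cost.** Wording only: no added visits, measurements or sample size, since the GMFM-88 is already planned. The downside is that a PEDI-only result will be read more cautiously.
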